#### Secondary outcomes

Insulin resistance would be measured by the Homeostasis Model of Assessment-Insulin Resistance (HOMA-IR) calculations based on fasting blood glucose and fasting serum insulin levels. Evaluation of β-cell function would occur in vivo (HOMA-B calculation) and in vitroAnthropometric assessment such as body weight, height, Body Mass Index (BMI), waist circumference (WC) and hip circumference (HC)Measurement of systolic blood pressure (SBP) and diastolic blood pressure (DBP)Measurement of lipid profile (total cholesterol, LDL cholesterol, HDL cholesterol and TAG)

#### Safety Assessment Index

The following information will be recorded/measured for the safety assessment: vital signs, general medical examination, kidney function tests, liver function tests (aspartate aminotransferase (AST), alanine aminotransferase (ALT), prothrombin time/International Normalized Ratio (PT/INR)) and adverse events. Liver profile and kidney profile will be done at the screening visit (visit 0), 2 months (visit 2) and at the completion of the study (visit 4).

### Procedures

#### Recruitment

Patients will be recruited on a voluntary basis from a cohort of patients with diabetes mellitus who are attending the Medical Clinic, University Medical Unit at the National Hospital of Sri Lanka. Those who consent to participate in the trial will visit the trial site voluntarily.

#### Study schedule

This involves measuring HbA_1_c, FPG and serum insulin according to the schedule described in Fig. 1. In addition, serum lipid profile (total cholesterol, triglycerides, LDL cholesterol and HDL cholesterol), liver profile (AST, ALT and PT/INR) and kidney profile (blood urea and serum creatinine) would be measured at baseline, 2 months and on completion of the study. The details of items which will be measured at every visit are described in Fig. 1.

### Measurement tools

#### Anthropometric measurements

Height will be measured using Harpenden pocket stadiometers (Chasmors Ltd., London, UK) to the nearest 0.1 cm. Body weight will be measured in light, indoor clothing to the nearest 0.1 kg using a SALTER 920 digital weighing scale (Salter Ltd., Tonbridge, UK). Waist circumference will be measured at midway between the iliac crest and the lower costal margin at the end of normal expiration using a flexible, plastic tape to the nearest 0.1 cm. Similarly, the HC also will be measured at widest part of the buttocks at the intertrochanteric level to the nearest 0.1 cm. All anthropometric measurements will be made by trained personnel.

#### Dietary measurements

A culturally validated Food Frequency Questionnaire (FFQ) will be used to obtain habitual intake of calories, macronutrients and micronutrients [23].

#### Physical activity

Physical activity will be evaluated by using the International Physical Activity Questionnaire (IPAQ) short version [24].

#### Clinical examination

Seated blood pressure is to be recorded on two occasions after at least a 10-min rest using an Accoson mercury sphygmomanometer (Accoson Healthcare, Asia-Pacific Region, Singapore).

#### Other

In addition to the above data, sociodemographic data, drugs and data on side effects will also be gathered via a questionnaire.

### Compliance calculation

Subjects are asked to return any remaining drugs and their compliance will be evaluated by using the formula given below:$$ \mathrm{Compliance}\left(\%\right)=\left[\left(\mathrm{distributed}\kern0.17em \mathrm{drugs}-\mathrm{remaining}\kern0.17em \mathrm{drugs}\right)/\mathrm{distributed}\kern0.17em \mathrm{drugs}\times 100\right] $$

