### Study design and setting

The study will be a phase-II/III, randomized, double-blind, placebo-controlled clinical trial. It will be conducted at the Medical Clinic, University Medical Unit, National Hospital of Sri Lanka for a period of 4 months, assessing the effects of the daily supplementation of capsules containing *Cinnamomum zeylanicum* in patients with type-2 diabetes mellitus. The Medical Clinic, University Medical Unit, National Hospital of Sri Lanka has around 400–500 patients with diabetes, attending the clinic on a monthly basis. The clinic operates 2 days per week and during all 4 weeks of a month. The duration of the trial will be 4 months, based on the evidence from previous research conducted by the investigators, and this duration is expected to be sufficient to identify changes in the primary glycemic outcomes (glycosylated hemoglobin (HbA1c), fasting plasma glucose (FPG) and serum insulin) assessed during the clinical trial [21].

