#### Suspension criteria

Subject’s demand to discontinue the studySerious adverse events or unusual changes in clinical test resultsPrincipal investigator’s decision to terminate the study (low rates of compliance, complications or inability to tolerate the study for various reasons)

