### Interventions

The treatment drug is a capsule containing *Cinnamomum zeylanicum* extract as the active ingredient; it will have a white-colored body and a capsules. Two doses of cinnamon will be used in the present study (250 mg and 500 mg) based on data arising from previous research [17, 21]. Stem bark of *Cinnamomum zeylanicum* will be extracted to distilled water using Soxlet apparatus and the resulting hot-water extract will be freeze-dried to obtain a crude water extract from which the capsules will be prepared. The placebo capsule will contain lactose monohydrate and stearic acid. The weight of each cinnamon oral capsule will be 300 mg (cinnamon + inert filler material). The placebo oral capsule will be identical in shape, size, weight and texture to the *Cinnamomum zeylanicum* oral capsule. In order to mask the aroma, cinnamon quills would be put into packets containing both the placebo and cinnamon capsules. Each group would be given two oral capsules before breakfast for daily usage for a period of 4 months (Table 1). Capsules will initially be given at visit 0 for a period of 1 month, and subsequently a monthly supply will be given to participants at each clinic visit.

**Table 1 Tab1:** Study groups in the clinical trial

Group	Number of capsules (1 = 250 mg of cinnamon)		
	Cinnamon	Placebo	Total
Group 1 (250 mg of cinnamon)	1	1	2
Group 2 (500 mg of cinnamon)	2	0	2
Group 3 (placebo)	0	2	2

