### Study period

The study will be for a period of 4 months and the visits and the evaluations will be done as follows: screening (visit 0), 1 month (visit 1), 2 months (visit 2), 3 months (visit 3) and 4 months (visit 4) (Fig. 1).

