### Statistical analysis

Parametric (e.g., ANOVA) and non-parametric (e.g., Kruskal-Wallis test) statistical tests will be applied using the SPSS version 14 (SPSS Inc., Chicago, IL, USA) and Stata/SE 10.0 (Stata Corporation, College Station, TX, USA) for the data analysis. Data will be entered by a minimum number of dedicated staff and saved in a dedicated computer with password protection. For each of the outcomes, multilevel regression analysis will be used to examine differences between trial arms. For binary outcomes the model will be logistic and, for continuous outcomes, the model will be linear regression. All analyses will follow intention-to-treat principles and a prespecified analysis plan. Where appropriate, sensitivity analyses will be conducted (for example, control for additional covariates; and bootstrapped *p* values for skewed outcomes). In the case of missing data values, we will apply mean imputation and regression imputation where rates are low, and consider multiple imputations where they exceed 10%. Since multiple tests are performed simultaneously, a Bonferroni correction will be made during analysis to determine the critical *P* value for significance.

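### The compliance formula divides by capsules distributed rather than capsules due, so it misstates adherence whenever the visit interval differs from the days supplied

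*Protocol article*

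**What the plan says.** The Compliance calculation section of the protocol article fixes the measure: "Subjects are asked to return any remaining drugs and their compliance will be evaluated by using the formula given below". The formula is (distributed − remaining) / distributed × 100. It has no term for days elapsed or capsules due. The section does not say whether the figure is computed per visit or over the whole trial, or how an unreturned pack is counted.

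The dosing and supply come from Interventions: "Each group would be given two oral capsules before breakfast for daily usage for a period of 4 months", with one month's capsules at visit 0, and "subsequently a monthly supply will be given to participants at each clinic visit". No capsule count per pack is given. Study period sets monthly visits up to month 4 without a window. Study design and setting adds that "The clinic operates 2 days per week and during all 4 weeks of a month".

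Compliance is used in one other place. Suspension criteria lists, as grounds for the principal investigator's decision to terminate, "low rates of compliance, complications or inability to tolerate the study for various reasons", with no percentage attached. Statistical analysis states that "All analyses will follow intention-to-treat principles and a prespecified analysis plan", and the article defines no analysis set by compliance.

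**The concern.** A pill count measures adherence when capsules taken are compared with capsules that should have been taken. Dividing by the quantity handed out makes the result depend on the date of attendance as well as on what the patient took. Someone who comes early necessarily brings capsules back and loses marks for it. Someone who comes late has had extra days in which to use the pack, and any days without capsules do not count.

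Off-schedule attendance is plausible here. A clinic open two days a week cannot always see a patient on the day the pack runs out, and no window limits the departure. At stake are the accuracy of the adherence the trial will report and the soundness of the one number the article offers to inform a judgement that compliance is low.

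**Working it through.** The article states no compliance figure, so there is none to reproduce. The check compares its formula with capsules taken over capsules due.

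**Inputs**
- Capsules per day: 2 in every arm (Interventions and Table 1).
- Pack size: not stated. Assumed 60 (30 days), with a range of 56 to 62 (28 to 31 days).
- Visit day: not fixed beyond monthly. Days 26, 28 and 35 are illustrations.
- Every capsule not returned is assumed taken, for both measures.

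**Formulas.** Let T be capsules taken, D capsules distributed, d days since dispensing and s = D/2 days supplied.
- Article: F = T / D × 100
- Due-based: A = T / (2d) × 100
- Hence F = A × d/s. The two agree only when d = s. F is too low when d < s and too high when d > s.

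**60-capsule pack**
- Day 28, every dose taken: F = 56/60 = 93.3%; A = 56/56 = 100%.
- Day 26, every dose taken: F = 52/60 = 86.7%; A = 52/52 = 100%.
- Day 35, pack emptied: F = 60/60 = 100%; A = 60/70 = 85.7%.
- Day 35, 70% of doses taken (49 of 70): F = 49/60 = 81.7%; A = 49/70 = 70.0%.

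**Sensitivity to pack size**

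| Case | Measure | 56 capsules | 60 capsules | 62 capsules |
|---|---|---|---|---|
| Day 26, all taken | Article | 92.9% | 86.7% | 83.9% |
| | Due-based | 100% | 100% | 100% |
| Day 28, all taken | Article | 100% | 93.3% | 90.3% |
| | Due-based | 100% | 100% | 100% |
| Day 35, pack emptied | Article | 100% | 100% | 100% |
| | Due-based | 80.0% | 85.7% | 88.6% |
| Day 35, 49 of 70 taken | Article | 87.5% | 81.7% | 79.0% |
| | Due-based | 70.0% | 70.0% | 70.0% |

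The direction depends only on whether d is below or above s; pack size changes the amount. With a 28-day pack and a visit at day 28, the error is nil.

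**Ranking.** With 60 capsules, a patient who missed nothing and came at day 26 (86.7%) ranks below one who had five days without capsules and came at day 35 (100%).

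**Whole trial**
- Off-setting visits: day 28 with 4 returned, then 32 days later with an empty pack. Article: (120 − 4)/120 = 96.7%. Due-based: 116/(2 × 60) = 96.7%. The error cancels.
- Visits every 28 days with four 60-capsule packs (112 days followed, 120 supplied), every dose taken. Article: 224/240 = 93.3%. Due-based: 224/224 = 100%. The error stays.

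**The case against.** The best defence is that the formula is a conventional pill count and is exact on schedule: a monthly supply with monthly visits makes distributed equal to due. If compliance is computed once over the trial, early and late visits offset each other, and nothing is left when total days equal days supplied. The pack size and visit days above are assumptions, and nothing in the article shows how often patients will attend off schedule. All of this stands, and it limits the point to off-schedule intervals and a net departure in total follow-up. It does not rescue the formula, because the article neither sets a window nor confines the calculation to the whole trial.

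A reader might infer four stronger things, none of which the document supports:
- **That punctual patients are penalised.** They are not. A fully adherent patient seen when the supply ends scores 100%. Likewise, a late attender scores exactly 100% only if the pack is empty.
- **That unreturned packs score 100% because of the denominator.** The article does not say such a pack counts as zero remaining. If it did, the fault would lie in the numerator: an on-time unreturned 60-capsule pack gives 60/60 = 100% with either denominator.
- **That participation would be ended for the wrong patients.** No threshold is stated, the decision is discretionary with several grounds, and the criterion does not cite this percentage. The figure could inform that decision, but no more can be said.
- **That a null HbA1c result could not be interpreted.** The analysis is by intention to treat, compliance defines no stated analysis set, and a pill count cannot prove ingestion under either denominator.

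**Conclusion.** The formula uses the wrong denominator for visits that do not coincide with the end of the supply. Its score is the due-based figure multiplied by days elapsed over days supplied. Under the 60-capsule assumption, that is 6.7 points too low at day 28 and 13.3 too low at day 26 for a fully adherent patient. At day 35 it is 14.3 points too high for an emptied pack and 11.7 too high at 70% dosing. The direction follows from the formula alone, while the sizes rest on the assumed pack count and visit days. Over the trial, the error persists only to the extent that total follow-up departs from total days supplied.

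The consequence is confined to the adherence the trial reports and to any use of that figure in the discretionary decision under Suspension criteria. The randomised comparison is unaffected. This is a minor point, worth correcting because correction is nearly free.

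**What to change.** Replace the formula in Compliance calculation with:

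compliance (%) = (capsules dispensed − capsules returned) / (2 × days since previous dispensing) × 100

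Compute it for each visit interval. For the whole treatment period, divide summed capsules by 2 × total days. The multiplier 2 applies in all three arms.

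As a separate safeguard for the numerator, record an unreturned pack as compliance unknown, not as zero remaining. The new denominator does not deal with this by itself.

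Wherever the compliance percentage is reported or consulted, use the revised figure. No compliance threshold or suspension rule is proposed here.

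The cost is that dispensing and visit dates must enter the calculation. The article does not list them as recorded items, but dispensing takes place at scheduled visits, and capsule counts are already needed for the present formula. The revised figure can exceed 100% (an empty 60-capsule pack at day 28 gives 60/56 = 107.1%). Such values should be kept and queried, not truncated. No patients or procedures are added. Trial status reports that enrolment had not started, so the change could precede the first count.

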### Statistical analysis

Parametric (e.g., ANOVA) and non-parametric (e.g., Kruskal-Wallis test) statistical tests will be applied using the SPSS version 14 (SPSS Inc., Chicago, IL, USA) and Stata/SE 10.0 (Stata Corporation, College Station, TX, USA) for the data analysis. Data will be entered by a minimum number of dedicated staff and saved in a dedicated computer with password protection. For each of the outcomes, multilevel regression analysis will be used to examine differences between trial arms. For binary outcomes the model will be logistic and, for continuous outcomes, the model will be linear regression. All analyses will follow intention-to-treat principles and a prespecified analysis plan. Where appropriate, sensitivity analyses will be conducted (for example, control for additional covariates; and bootstrapped *p* values for skewed outcomes). In the case of missing data values, we will apply mean imputation and regression imputation where rates are low, and consider multiple imputations where they exceed 10%. Since multiple tests are performed simultaneously, a Bonferroni correction will be made during analysis to determine the critical *P* value for significance.

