### Sample size

The sample size was calculated using one-way analysis of variance (ANOVA), by the formula given below;$$ {n}_A=\left({\sigma^2}_A+{\sigma^2}_B/\kappa \right){\left(\frac{z_1{{{{}_{-}}_{\alpha}}_{/}}_{\tau }+{{z_1}_{-}}_{\beta }}{\mu_A-{\mu}_B}\right)}^2 $$

*n*
_*A*_ – sample size in one group
*σ*
_*A*_ – standard deviation of group A
*σ*
_*B*_ – standard deviation of group B
*κ* – sampling ratio
*α* – type-I error
*τ* – number of pairwise comparisons
*β* – type-II error
*μ*
_*A*_ – mean of group A
*μ*
_*B*_ – mean of group B

The number of patients required in a group for determination of a 0.75% reduction of HbA_1_c in a treatment group (*μ*
_*A*_
*–* 7.5%), in comparison with the placebo group (*μ*
_*B*_
*–* 6.75%) at 80% power (*β*), 95% confidence level (*α* – 0.05), for three pairwise comparisons (*τ*), with a sampling ratio of 1 (*κ*) is 62 in one group according to the above formula. The standard deviation of the HbA_1_c (*σ*
_*A*_ and *σ*
_*B*_) was taken as 1.4 based on evidence from previous research among Sri Lankan patients with diabetes [22]. Hence, the total sample required for the three groups will be 186. Therefore, a total of 210 subjects with diabetes in three equal groups will be recruited for the study, allowing for a dropout rate of 10%. Subjects will be randomly and equally assigned into two test groups (*n* = 70 each) and will receive either a *Cinnamomum zeylanicum* oral capsule (250 mg or 500 mg) or an identical placebo daily for 4 months.

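### At low rates of missing data, outcomes are to be filled in by single mean or regression imputation, which understates the standard error or shrinks the estimated effect, depending on how it is done

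*Protocol article*

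**What the plan says.** The Statistical analysis section of the protocol article fixes the handling of missing values in one sentence: "we will apply mean imputation and regression imputation where rates are low, and consider multiple imputations where they exceed 10" percent. The first half is a commitment. The second half only says that multiple imputation will be thought about. Nothing restricts the rule to covariates, so it reaches the primary outcomes (HbA1c, fasting plasma glucose and insulin). The text does not say whether means or regressions are taken within arm or across arms, or how the extra uncertainty enters the standard error.

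The same section names the analysis model ("For each of the outcomes, multilevel regression analysis will be used to examine differences between trial arms") and the analysis principle ("All analyses will follow intention-to-treat principles and a prespecified analysis plan"). The Sample size section sets recruitment at 210, "allowing for a dropout rate of 10" percent.

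**The concern.** A single imputed value is analysed as if it had been observed. If it is the mean of the patient's own arm, it adds to the sample size and nothing to the spread, so the standard error comes out too small and the test rejects too often. If it is the mean over all arms, each imputed patient contributes no treatment difference, so the estimate is pulled towards zero. Regression imputation splits in the same way, according to whether arm is in the prediction model.

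The protocol itself chooses this method, so it is not a detail left open for the analysis plan; a plan that followed the protocol would inherit the fault. Two things are at stake: the type-I error of the HbA1c comparison, which the promised Bonferroni correction is meant to protect, or the size of the reported effect.

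**Working it through.** **Inputs from the Sample size section.** Difference 0.75 ("The number of patients required in a group for determination of a 0.75% reduction" in HbA1c); SD 1.4 ("was taken as 1.4 based on evidence from previous research among Sri Lankan patients with diabetes"); α = 0.05 ("95% confidence level"); τ = 3 ("for three pairwise comparisons"); power 80%; 70 recruited per arm.

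**The plan's own figure.** The printed formula uses z(1−α/τ):

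n = 2 × 1.4² × ((2.128 + 0.842)/0.75)² = 61.46, so 62 per group and 186 in all.

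Dividing by 0.9 gives 186/0.9 = 206.7, so 207. The planned 210 tolerates a loss of 24/210 = 11.4%. The 62 is reproduced. (The formula does not halve α for a two-sided test; that is a separate matter and has no bearing here.)

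**Assumptions of the illustration.** Two arms of n = 70, k missing per arm completely at random, o = n − k observed, and an unadjusted two-sided t test. The Bonferroni level is taken as 0.05/3 = 1.67%, using the three comparisons of the sample size.

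**Arm-mean imputation.** The estimate stays unbiased.

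- True SE = 1.4 × √(2/o).
- Reported SE = 1.4 × √((o−1)/(n−1)) × √(2/n).
- Ratio r = √((o−1)/(n−1)) × √(o/n).
- Type-I error = P(|t with 2o−2 df| > r × t_crit). With 138 df, t_crit is 1.977 at 5% and 2.424 at 1.67%.

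For k = 7, r = √(62/69) × √(63/70) = 0.899. The reported SE is 0.224 against a true 0.249. The effective cut-off is 0.899 × 1.977 = 1.778 on 124 df, which gives 7.8%.

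**Pooled-mean imputation.** The expected difference is 0.75 × o/n.

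| Missing per arm | SE ratio, arm mean | Type-I error at 5%, arm mean | Type-I error at 1.67%, arm mean | Expected difference, pooled mean |
|---|---|---|---|---|
| 1 of 70 | 0.986 | 5.3% | 1.8% | 0.74 |
| 4 of 70 | 0.942 | 6.5% | 2.4% | 0.71 |
| 7 of 70 | 0.899 | 7.8% | 3.1% | 0.68 |

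Simulation (40,000 trials per case) gives type-I error of 6.2% and 7.7% for arm means with 4 and 7 missing, close to the formula. For pooled means with 7 missing it gives type-I error of 5.1%, and power at a true 0.75 of 0.850 against 0.846 for observed cases only. Estimate and standard error shrink together, so the test hardly changes.

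**Regression imputation.** These are simulated results with 7 of 70 missing, values predicted without a random residual, and an assumed baseline–outcome correlation of 0.6. The document gives no correlation and only this value was run. With no correlation, the prediction reduces essentially to the mean, so the mean-imputation results mark that end.

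- Arm in the model: difference 0.75. Unadjusted, reported SE 0.228 against 0.245 and type-I error 6.7%. Baseline-adjusted, 0.180 against 0.201 and 7.9%.
- Arm not in the model: difference 0.67, type-I error 4.9% unadjusted and 5.0% adjusted.

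**Observed data only, 7 of 70 missing.** Difference 0.75, reported SE 0.249 against 0.250, type-I error 5.15%, which is the nominal level within simulation error.

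**The case against.** Four points on the other side have force.

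- **The largest figures are a ceiling.** The rule applies at low rates, and low is not defined; 10% is only the point above which multiple imputation is considered. With 1 or 2 of 70 missing, type-I error is about 5.3% to 5.7%. The 10% in the sample size is a recruitment allowance, and 210 tolerates 11.4%, so a slightly larger loss would move into the range where multiple imputation is considered. This stands, and the size is therefore given as a range.
- **The two harms are alternatives.** A reader might infer that the HbA1c test will both reject too often and understate the effect. It cannot do both through this mechanism. The inflated error needs a within-arm reading that the text does not state, and the pooled reading leaves the test intact. But each reading damages something, so the ambiguity does not rescue the rule.
- **The illustration is not the planned analysis.** A reader might take 7.8% as this trial's error rate. The document does not support that: the plan is a multilevel model with several visits, and the figures come from an unadjusted comparison at one time point. They show direction and rough size.
- **Single imputation is not harmful everywhere.** For missing baseline covariates it does far less damage, so a ban there would go too far.

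One might also infer a further bias from outcome-related dropout. That is plausible, but nothing in the document allows it to be sized, and it is not part of this point. Nor is the lack of a missing-not-at-random analysis, which a protocol article may leave to the analysis plan.

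**Conclusion.** The rule is wrong as written for outcome variables and should be fixed; the damage is moderate. Up to 10% missing, either type-I error at nominal 5% rises to between about 5.3% and 7.8% (up to about 3.1% at nominal 1.67%), or the estimated difference shrinks by the missing share, at most from 0.75 to about 0.68. The first follows from imputing within arm or with arm in the regression, the second from imputing across arms. The anticipated 10% loss lies at the upper edge of the single-imputation range, and above it multiple imputation is still only a possibility.

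This rests on data missing completely at random, equal loss in both arms, SD 1.4, an unadjusted two-arm test and, for the regression results, a correlation of 0.6. The direction of the fault does not depend on the SD. The sensitivity analyses that the section names as examples (extra covariates, bootstrapped p values) do not address it.

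**What to change.** For outcome variables, remove single mean and regression imputation at every rate of missingness. Fit the multilevel linear model that is already planned to all observed outcome data, without filling in values first. Where an outcome does need imputation, use multiple imputation whatever the rate, with arm, baseline value, stratification factors and any earlier visits in the imputation model. Simple imputation may stay for missing baseline covariates.

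How much the model recovers from patients who leave early depends on how often HbA1c is measured. That schedule is given only in Fig. 1, which was not available for this review. If HbA1c is measured only at baseline and 4 months, the model recovers little for it, but the recommendation is unchanged.

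The cost is a change of wording and a little programming. Standard errors will be slightly larger than under arm-mean imputation, and correct. The article states that enrollment had not begun, so the change could be made before any data are seen.

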### Study groups

#### Treatment groups

To evaluate a dose-response relationship, the phase-II study will include two treatment groups. The groups will receive *Cinnamomum zeylanicum* doses of either 250 mg or 500 mg based on results arising from previous research:Group 1 – *Cinnamomum zeylanicum* dose 250 mg dailyGroup 2 – *Cinnamomum zeylanicum* dose 500 mg daily

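### The planned Bonferroni correction is valid but needlessly conservative: Holm's procedure over the same tests controls the same error and never rejects less

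*Protocol article*

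**What the plan says.** The Statistical analysis section of the protocol article sets the multiplicity rule in one sentence: "Since multiple tests are performed simultaneously, a Bonferroni correction will be made during analysis to determine the critical *P* value for significance". It gives neither the family of tests nor the divisor. The same section names ANOVA and Kruskal-Wallis as examples of tests and regression models for comparing the arms. It does not make an overall test a condition for the pairwise ones.

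The Sample size section shows one family the authors had in mind. It divides alpha by the number of arm comparisons and reports that the requirement "for three pairwise comparisons (*τ*), with a sampling ratio of 1 (*κ*) is 62 in one group". The Treatment groups section gives the reason for two doses: "To evaluate a dose-response relationship, the phase-II study will include two treatment groups". The Primary outcome index section lists three primary outcomes (HbA1c, FPG and serum insulin), so the correction may be meant to cover arms, outcomes or both.

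**The concern.** Bonferroni holds every test to the strictest threshold, even after other hypotheses in the family have been rejected. A step-down rule relaxes the threshold as rejections accumulate and gives the same family-wise guarantee. The single-step rule therefore gives up some power without any gain in error control.

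What is at stake is mainly the second claim. This design wants to say something about both doses, and the comparison with the larger p-value (often 250 mg, if the response is graded) is the one a single-step rule penalises.

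**Working it through.** **Inputs.** From Sample size: difference 0.75 ("determination of a 0.75% reduction of HbA_1_c in a treatment group"); SD 1.4 in each group (it "was taken as 1.4 based on evidence from previous research among Sri Lankan patients with diabetes"); alpha 0.05; three comparisons; power 80%; 62 per arm ("Hence, the total sample required for the three groups will be 186"). Two inputs are assumptions: two-sided tests, because the text does not state sidedness, and the effect of the second dose, which is not given and is therefore varied.

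**Step 1: the plan's own figure.** The printed formula is n = (σ² + σ²)·[(z(1−α/τ) + z(1−β))/Δ]². With z(1−0.05/3) = 2.128 and z(0.80) = 0.842:

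n = 3.92 × (2.970/0.75)² = 61.5, so 62.

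The stated figure reproduces, as a one-sided 0.05/3 calculation. With two-sided tests at 0.05/3 the critical value is 2.394. Power at 62 per arm is then Φ(0.75/(1.4·√(2/62)) − 2.394) = Φ(2.983 − 2.394) = 72% (71% by simulation with t tests).

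**Step 2: why Holm cannot reject less.** Order the p-values and compare them with 0.05/3, 0.05/2 and 0.05, stopping at the first failure. No threshold is below 0.05/3, so every Bonferroni rejection is kept. For error control, if m₀ hypotheses are true, the first true one reached is tested at no more than 0.05/m₀, so the Bonferroni inequality over those m₀ gives at most 5%. This needs no assumption about correlation, and it holds for any family size: three arm comparisons, three outcomes, or nine tests. The first step is identical to Bonferroni, so the chance of at least one rejection is the same.

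**Step 3: size of the gain on HbA1c.** Simulation with 400,000 trials per scenario, three normal arms of 62, SD 1.4, pooled variance with 183 df, two-sided tests. Monte Carlo error is at most √(0.25/400,000) = 0.08 points. The overall-test column means an F test at 0.05 and then, only if it is significant, pairwise tests at 0.05.

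| Scenario and result | Bonferroni | Holm | Overall test first |
|---|---|---|---|
| Both doses 0.75: each dose vs placebo | 71.4% | 74.6% | 80.8% |
| Both doses 0.75: both shown superior | 57.5% | 63.9% | 74.3% |
| Both doses 0.75: any significant pair | 85.3% | 85.3% | 87.4% |
| Graded 0.375/0.75: 250 mg vs placebo | 18% | 23% | 31% |
| Graded 0.375/0.75: 500 mg vs placebo | 71.4% | 72.1% | 74.9% |
| Family-wise error, all arms equal | 4.4% | 4.4% | 5.0% |
| Family-wise error, one arm different | 1.7% | 3.4% | 5.0% |

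At the 70 per arm to be randomised, with both doses at 0.75, Bonferroni gives 77.4% and Holm 80.4% per comparison, so the gain stays at about 3 points.

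**Step 4: limits of the overall-test-first route.** With exactly three arms, two true pairwise nulls imply that all three means are equal. The procedure is therefore closed, and strong control holds within one outcome. It does not protect across outcomes. Run at 0.05 on each of three independent primary outcomes, it gives 1 − 0.95³ = 14.3% under the global null. At assumed correlations of 0.3, 0.5 and 0.7 the error is about 13.7%, 12.7% and 10.9%.

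**The case against.** The strongest reply is that nothing here is wrong. Bonferroni is valid, simple and fixed in advance. It matches the alpha division used to size the trial, and it comes with simultaneous confidence intervals that agree with the tests. That stands: this is not an error, and the intervals are a real if small advantage. The reply does not rescue the choice as a testing rule, because Holm covers the same family with the same guarantee and loses no rejection.

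A reader might infer something stronger: that Bonferroni should give way to an overall test with pairwise tests at 0.05, for about 10 points of power at no cost. The documents do not support that, for four reasons.

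- The multiplicity sentence names no family. Reading it as arm comparisons only is an inference from the Sample size section, and there are three primary outcomes. Giving HbA1c the full 0.05 could remove a protection that the sentence was meant to provide.
- The gain of about 9 points (80.8 − 71.4 = 9.4) needs both doses, or only one, to reach 0.75. Under the graded response it is about 3.5 points for 500 mg (74.9 − 71.4), and about 2 for finding any difference.
- A non-significant overall test can block a comparison that Bonferroni would have declared. This happened in 0.2% to 0.5% of simulated trials with a true effect.
- ANOVA appears only as an example of a test, not as a gate.

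It is also fair to object that power below the stated 80% comes from the sidedness of the sample-size formula. That is a separate matter. Holm's advantage over Bonferroni does not depend on it, although the percentages above do.

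**Conclusion.** The point holds as an efficiency improvement. Over whatever family the plan intends, Holm is at least as powerful as the stated rule and gives the same error guarantee. For the three HbA1c arm comparisons the gain is about 3 points per comparison and about 6 points for showing both doses superior, if both reach 0.75. Under the assumed graded response it is about 5 points for 250 mg and less than 1 for 500 mg. There is no gain in the chance of finding at least one difference.

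These figures rest on 62 evaluable patients per arm, SD 1.4, normal data and two-sided tests. They also take the family to be the three arm comparisons on one outcome. In a larger family the direction is the same but the size differs. It would be wrong to conclude that the planned correction is invalid, or that it can be dropped in favour of unadjusted pairwise tests without a correction across outcomes.

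**What to change.** Replace the Bonferroni sentence with one along these lines: *Family-wise error will be held at two-sided 0.05 by Holm's step-down procedure over the following tests: [list the arm comparisons and primary outcomes in the family].* Two-sided is the assumption used here; the sponsor should confirm it when writing the sentence.

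If the sponsor prefers the overall-test-first route for the arm comparisons within an outcome, the correction across HbA1c, FPG and insulin must be kept, for example by running the overall and pairwise tests at 0.05/3 for each outcome.

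The cost is one sentence, and the protocol article reports that enrolment has not begun. Holm has no simple simultaneous confidence intervals that match its decisions. If intervals are reported, the text should say whether they are unadjusted or Bonferroni-adjusted, and that they need not agree with the Holm decisions.
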